## LIST OF ABBREVIATIONS AND RELEVANT DEFINITIONS

|                |                                                                                                                                                                                                                               |
|----------------|-------------------------------------------------------------------------------------------------------------------------------------------------------------------------------------------------------------------------------|
| ABR     | General Assessment and Registration form (ABR form), the application form that is required for submission to the accredited Ethics Committee; in Dutch: Algemeen Beoordelings- en Registratieformulier (ABR-formulier) |
| AE      | Adverse Event                                                                                                                                                                                                          |
| AR      | Adverse Reaction                                                                                                                                                                                                       |
| CA      | Competent Authority                                                                                                                                                                                                    |
| CCMO    | Central Committee on Research Involving Human Subjects; in Dutch: Centrale Commissie Mensgebonden Onderzoek                                                                                                            |
| CV      | Curriculum Vitae                                                                                                                                                                                                       |
| DSMB    | Data Safety Monitoring Board                                                                                                                                                                                           |
| EU      | European Union                                                                                                                                                                                                         |
| EudraCT | European drug regulatory affairs Clinical Trials                                                                                                                                                                       |
| GCP     | Good Clinical Practice                                                                                                                                                                                                 |
| GDPR    | General Data Protection Regulation; in Dutch: Algemene Verordening Gegevensbescherming (AVG)                                                                                                                           |
| IB      | Investigator's Brochure                                                                                                                                                                                                |
| IC      | Informed Consent                                                                                                                                                                                                       |

|                |                                                                                                                                                                                                                                                                                                                                                  |
|----------------|--------------------------------------------------------------------------------------------------------------------------------------------------------------------------------------------------------------------------------------------------------------------------------------------------------------------------------------------------|
| IMP     | Investigational Medicinal Product                                                                                                                                                                                                                                                                                                         |
| IMPD    | Investigational Medicinal Product Dossier                                                                                                                                                                                                                                                                                                 |
| METC    | Medical research ethics committee (MREC); in Dutch: medisch-ethische toetsingscommissie (METC)                                                                                                                                                                                                                                            |
| (S)AE   | (Serious) Adverse Event                                                                                                                                                                                                                                                                                                                   |
| SPC     | Summary of Product Characteristics; in Dutch: officiële productinformatie IB1-tekst                                                                                                                                                                                                                                                       |
| Sponsor | The sponsor is the party that commissions the organisation or performance of the research, for example a pharmaceutical company, academic hospital, scientific organisation or investigator. A party that provides funding for a study but does not commission it is not regarded as the sponsor, but referred to as a subsidising party. |
| SUSAR   | Suspected Unexpected Serious Adverse Reaction                                                                                                                                                                                                                                                                                             |
| UAVG    | Dutch Act on Implementation of the General Data Protection Regulation; in Dutch: Uitvoeringswet AVG                                                                                                                                                                                                                                       |
| WMO     | Medical Research Involving Human Subjects Act; in Dutch: Wet Medisch-wetenschappelijk Onderzoek met Mensen                                                                                                                                                                                                                                |

## SUMMARY

**Rationale:** Iodine has germicidal properties and contributes to the defense mechanism against pathogens. In addition, iodine has anti-inflammatory and immune-modulating properties that may have a beneficial effect in the treatment of COVID-19 infections. This leads to our hypothesis that iodine is effective in the treatment of COVID-19 disease.

**Objective:** To demonstrate that iodine treatment has a beneficial effect on the course of COVID-19 disease. Beneficial effect is defined as a reduced risk of deterioration, such as transfer from a regular ward to the ICU, death in the regular ward, or death in the ICU.

**Study design:** Open-label randomized trial with a control group.

**Study population:** All patients aged 18 years and older who are admitted to the hospital and test positive for SARS-CoV-2 infection will be recruited for the study. Patients must be mentally competent and able to read the patient information sheet and sign the informed consent form.

**Intervention:** Patients in the intervention group will receive, for 8 consecutive days, once daily, ¼ Potassium Iodide 65 mg tablet. The control group will receive no supplement and no placebo.

**Main study parameters/endpoints:**

Primary endpoint: clinically relevant deterioration. Deterioration is defined as:

1. From baseline on regular ward to ICU
2. From baseline on regular ward and death
3. From baseline in ICU and death

**Secondary endpoint:** total number of days of hospital admission and total number of deaths.

**Nature and extent of the burden and risks associated with participation, benefit and group relatedness:** When a patient is randomized and placed in the treatment group, a beneficial effect on the course of the COVID-19 infection is to be expected. The patient must then take ¼ Potassium Iodide 65 mg tablet once daily for 8 consecutive days. The risk, given the exclusion criteria, is very limited and in principle temporary.

## 1. INTRODUCTION AND RATIONALE

Iodine has a germicidal effect and contributes to the defense mechanism against pathogens [1]. The SARS-CoV-2 virus has, in addition to a protective protein shell, the capsid, an outer lipid membrane—the envelope—in which proteins are also anchored. Hemagglutinin (HA) is a surface protein that enables recognition of host cells and causes “injection” of the viral genome by inducing fusion of the endosomal membranes. Neuraminidase (NA) is another surface protein that ensures that virus particles, after replication in cells, can detach from these cells and spread further. It does this by cleaving sialic acid residues. Iodine reduces the virulence of viruses through interaction with various surface proteins. This leads to degeneration of the capsid and thereby to virus inactivation [14]. Additionally, iodine inhibits HA and NA activity, making it more difficult for the virus to enter the host cell and to spread outside the cell [16,17,21]. Iodine may also cause destabilization of the envelope through a reaction with unsaturated carbon compounds [15]. Iodine has antiviral properties against coronaviruses [22,23]. Recently, a chemical interaction has been described between iodine and the Coronavirus spike (S) protein, which facilitates fusion of the virus with the host cell, and with the ACE2 receptors. These findings strongly suggest a beneficial effect of iodine treatment in Coronavirus infections [27,28].

COVID-19 disease can be fatal as a result of an overreaction of the body’s immune system, called a cytokine storm. More pro-inflammatory cytokines are then produced, such as IL-2, IL-8, IFN-gamma, and TNF-alpha. Treatment with iodine at non-toxic dosages leads to a reduction of these cytokines [2,18,19]. Additionally, an excess of Reactive Oxygen Species (ROS, radicals) is produced, which are toxic to pathogens but at the same time can also be harmful to the body itself [20]. Neutralizing this excess of radicals with antioxidants can have a beneficial effect on the course of conditions associated with high oxidative stress [20]. Iodine is a strong antioxidant and neutralizes excess ROS [3,24].

Iodine is secreted via the mucous membranes in the mouth and trachea, partly via Sodium-Iodide symporters. Furthermore, there is a relationship between iodine status and the concentration of iodine in saliva [13,25]. Additionally, iodine has anti-inflammatory and immune-modulating properties that may have a beneficial effect in the treatment of COVID-19 infections [2,3]. In multiple case reports, a beneficial effect of iodine treatment in viral infections is described [4,5].

In epidemiological research into the number of deceased COVID-19 patients, a striking difference is found between Japan and Italy. On April 1, 2020, Japan had 57 deaths with 126 million inhabitants (0.5/million), and Italy had 12,428 deaths with 60 million inhabitants (207/million) [6]. Furthermore, Japanese people are known for their high iodine intake through food, in contrast to Italians who are iodine deficient. The iodine status, measured in Urinary Iodine Concentration (UIC) according to WHO criteria, is 282 mcg/L in Japan and 84 mcg/L in Italy [7,8,9]. These two findings suggest a protective effect of iodine against COVID-19 infections. This leads to our hypothesis that iodine is effective in the treatment of COVID-19 infections. To test the hypothesis, we want to conduct research into the treatment with iodine in COVID-19 infected patients.

## **2. OBJECTIVES**

**Primary endpoint:** Clinically relevant deterioration. Deterioration is defined as:

- From baseline on general ward to ICU
- From baseline on general ward and death
- From baseline in ICU and death

**Secondary endpoint:**

- Total number of days of hospital admission
- Total number of deaths

### **3. STUDY DESIGN**

Open-label randomized clinical trial with control group.

## **4. STUDY POPULATION**

### **4.1 Population**

Hospitalized patients with COVID-19 disease in Maxima MC.

### **4.2 Inclusion criteria**

All patients aged 18 years and older who test positive for SARS-CoV-2 infection may participate in this study.

### **4.3 Exclusion criteria**

Thyroid disorder or treatment such as goiter, thyroidectomy, radioactive iodine, medications related to thyroid dysfunction or Amiodarone. The investigator must have access to the medical history and medication use of the subject. If necessary, contact will be made with the general practitioner or other hospitals to obtain the required information. If no or insufficient data can be obtained, the subject cannot participate in the study.

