### **6.4 Summary of known and potential risks and benefits**

The likelihood of side effects is derived from the listings in the pharmacotherapeutic compass for Potassium Iodide 65 mg tablets. The side effects listed there are relatively mild and in principle transient. In rare cases, in patients with pre-existing thyroid disorders, thyrotoxicosis may occur. Temporary medicinal treatment may then be necessary to correct thyroid dysfunction. However, this is not expected since thyroid disorders or medication related to thyroid dysfunction are exclusion criteria. Previous studies show that administering relatively high doses of iodine is safe [10,11,12].

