#### **9.2.2 Serious adverse events (SAEs)**

A serious adverse event is any untoward medical occurrence or effect that:

- results in death;
- is life-threatening (at the time of the event);
- requires hospitalization or prolongation of existing hospitalization;
- results in persistent or significant disability or incapacity;
- is a congenital anomaly or birth defect; or
- any other important medical event that did not result in any of the outcomes listed above due to medical or surgical intervention but could have been based on appropriate judgment by the investigator.

An elective hospital admission will not be considered a serious adverse event.

The investigator will report all SAEs to the sponsor without undue delay after obtaining knowledge of the events, except for the following SAEs: not applicable.

The sponsor will report the SAEs through the web portal ToetsingOnline to the accredited METC that approved the protocol, within 7 days of first knowledge for SAEs that result in death or are life-threatening, followed by a maximum of 8 days to complete the initial preliminary report. All other SAEs will be reported within a maximum of 15 days after the sponsor has first knowledge of the serious adverse events.

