## **13. STRUCTURED RISK ANALYSIS**

**Risks of ingesting Potassium Iodide are minimal** [10,11,12]. Potassium Iodide tablets of 65 mg are distributed among the population living within a certain distance from a nuclear power plant, with the advice to take a one-time dose of 130 mg in case of a nuclear disaster. The goal is to prevent the uptake of radioactive iodine and thereby prevent thyroid cancer. These tablets are distributed indiscriminately. This is justified because the benefit/risk ratio is high—in other words, the risk of possible mild side effects does not outweigh the risks of developing thyroid cancer.

In the pharmacotherapeutic compass, side effects are described for two indications for Potassium Iodide treatment. In addition to the aforementioned, Potassium Iodide is also given as preparation for thyroid surgery. Dosages used range from 150 to 750 mg per day for 10 to 14 days. The total dosage then amounts to 1,500 mg to 10,500 mg. Even at these dosages, relatively few and mild side effects are described.

Additionally, the website [www.vergiftigingen.info](http://www.vergiftigingen.info) does not advise additional measures for adults who have ingested a one-time dose of  $10 \times 65 \text{ mg} = 650 \text{ mg}$  Potassium Iodide tablets, since no relevant side effects are expected (see appendix 1).

The Potassium Iodide dosage used in our study—16.5 mg per day for 8 days, totaling 130 mg—is safe and the risk of side effects is very limited. The potential benefit of treatment with iodine is substantial, namely a less severe course of COVID-19 disease, a shorter illness period, a greater chance of survival, and possibly less irreversible lung damage.

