### 13.1 Potential issues of concern

**The chance of thyrotoxicosis occurring is very small.** Should this nevertheless occur, the symptoms are temporary and transient.

**a. Level of knowledge about mechanism of action** The mechanism of thyrotoxicosis may cause hyperthyroidism due to autonomous dysregulation of the thyroid. It may also temporarily cause hypothyroidism due to blockage of iodine uptake by the thyroid.

**b. Previous exposure of human beings with the test product(s) and/or products with a similar biological mechanism** In previous studies, no relevant side effects were reported at the dosage and administration frequency used in our study [10,11,12].

**c. Can the primary or secondary mechanism be induced in animals and/or in ex-vivo human cell material?** Not known

**d. Selectivity of the mechanism to target tissue in animals and/or human beings** Not known

**e. Analysis of potential effect** Multiple in vitro studies and animal model studies have demonstrated virus inactivation by iodine.

**f. Pharmacokinetic considerations** Iodine is rapidly absorbed into the blood via the intestines. Iodine is actively taken up in the thyroid and is also relatively quickly excreted in various tissues such as mucous membranes.

**g. Study population** All patients aged 18 years and older who are admitted to the hospital and test positive for SARS-CoV-2 infection will be recruited for this study. Patients must be mentally competent and able to read the patient information sheet and sign the informed consent form.

**h. Interaction with other products** Not applicable

**i. Predictability of effect** It is expected that iodine will have a beneficial effect on the course of COVID-19 disease.

**j. Can effects be managed?** Should thyroid dysregulation occur in the very rare case, it is usually temporary and transient. If not, there are medications available to effectively treat this dysregulation.

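### Pregnant and breastfeeding adults are eligible for eight daily iodide doses, but the risk assessment covers only the participant

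*Protocol*

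**What the plan says.** Protocol section 4.2 sets entry broadly: "All patients aged 18 years and older who test positive for SARS-CoV-2 infection may participate in this study". Section 4.3 excludes on these conditions: "Thyroid disorder or treatment such as goiter, thyroidectomy, radioactive iodine, medications related to thyroid dysfunction or Amiodarone". It obliges the investigator to have the medical history and medication use, and adds one procedural exclusion: "If no or insufficient data can be obtained, the subject cannot participate in the study". The Summary, 11.3 and 13.1g add only mental competence and, in the Summary and 13.1g, the ability to read the information and sign consent.

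On risk, the Summary states: "The risk, given the exclusion criteria, is very limited and in principle temporary". Section 6.4 says of thyrotoxicosis: "However, this is not expected since thyroid disorders or medication related to thyroid dysfunction are exclusion criteria". Section 11.4 repeats that argument and, separately, calls the risk of side effects very limited at the dose used. Section 13 compares the course with much larger or single exposures. Section 13.1a adds a second thyroid effect of iodide: "It may also temporarily cause hypothyroidism due to blockage of iodine uptake by the thyroid".

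**The concern.** An eligibility rule and a risk assessment should describe the same people. Here the rule admits all adults apart from a thyroid-related list, while the assessment is written about the participant's own thyroid. For a pregnant or breastfeeding participant, a second individual is involved whom the assessment never mentions and whose thyroid history cannot be screened.

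At stake is whether the low-risk statement given to the ethics committee and to patients holds for everyone the protocol lets in. The endpoint and the analysis are not affected.

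**Working it through.** No statistical figure of the plan bears on eligibility, so the main check sets the sections side by side.

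**Step 1: who may enter.** Section 4.2 has two conditions, age 18 or older and a positive test. Section 4.3 removes patients with a thyroid disorder, thyroid treatment, thyroid-related medication, amiodarone, or a history that cannot be obtained. The Summary, 11.3 and 13.1g require competence and, except for 11.3, ability to consent. None of these concerns pregnancy or lactation, and no visible section mentions pregnancy, breastfeeding, contraception or a pregnancy test. Section 13.1g restates the population as all adults admitted with a positive test. These patients are therefore eligible under the stated rule.

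**Step 2: the exposure.** Section 5 gives a quarter of a 65 mg tablet once daily for 8 days: 65 / 4 = 16.25 mg potassium iodide per day, and 16.25 × 8 = 130 mg in total.

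**Step 3: what each risk statement rests on.**

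| Section | Claim | Stated basis | Whose risk |
|---|---|---|---|
| Summary | risk very limited and in principle temporary | the exclusion criteria | the participant |
| 6.4 | thyrotoxicosis not expected | the thyroid exclusions | the participant |
| 11.4 | risk of side effects very limited | the dose | the participant |
| 11.4 | thyrotoxicosis virtually ruled out | the thyroid exclusions | the participant |
| 13 | course is safe | dose, and comparison with other uses | the participant |
| 13.1a | hypothyroidism possible through blocked uptake | mechanism; no exclusion argument given | the participant |

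Only the Summary ties the overall low risk to the exclusion criteria. The reasoning for those criteria, in 6.4 and 11.4, concerns thyrotoxicosis in someone with existing thyroid disease. The effect in 13.1a is not tied there to existing disease, and no section argues that the exclusions prevent it.

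**Step 4: mention of offspring.** The only one is the item "is a congenital anomaly or birth defect; or" in 9.2.2. It belongs to a general definition of serious adverse events and does not restrict entry.

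**Step 5: size.** The documents give no share of pregnant or breastfeeding patients. I assume 0.5% to 2%. The total of 224 is from section 4.4, and its equal groups imply that half receive iodide.

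- Affected participants: 0.005 × 224 = 1.1 to 0.02 × 224 = 4.5.
- Allocated to iodide: 1.1 / 2 ≈ 0.6 to 4.5 / 2 ≈ 2.2.
- Chance of at least one among 224 / 2 = 112 iodide patients: 1 − 0.995^112 = 0.43 to 1 − 0.98^112 = 0.90.

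Making them ineligible would not change power, because recruitment would run to the same 224.

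**The case against.** The strongest reply is that no hazard to a fetus or infant appears in the documents. No section says that iodide reaches either of them or harms them, and 13.1j calls thyroid dysregulation usually temporary and otherwise treatable. This stands. A reader might infer that the protocol exposes a fetus or infant to a known danger; the text does not support that. The birth-defect item is a standard category and is no evidence of a recognised risk.

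A reader might also infer that the thyroid history is the protocol's only safeguard. It is not. Sections 11.4 and 13 also rely on the dose, the short course and comparison with larger exposures. Section 13 cites general distribution of tablets near nuclear plants, "with the advice to take a one-time dose of 130 mg in case of a nuclear disaster", and the trial course adds up to the same 130 mg. But that comparison concerns a single intake justified there by preventing thyroid cancer, and section 13 does not discuss pregnancy or lactation. The dose arguments therefore support low risk for the participant and leave the gap open.

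Nor should 6.4 and 11.4 be read as crediting the exclusion criteria with a very limited risk overall. Section 6.4 says only that thyrotoxicosis is not expected, and 11.4 attributes the very limited risk to the dose. Only the Summary makes the broader link.

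Finally, one can call this an omission, and say that the consent pages or product information, which are not visible, may deal with it. The second part cannot be ruled out. But 4.2 positively admits all adults, 4.2 and 4.3 appear complete, and wording elsewhere would not amend them or section 13.

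**Conclusion.** The concern holds as a mismatch within the protocol. Sections 4.2 and 4.3 let pregnant and breastfeeding adults be randomised to eight daily iodide doses, while the Summary, 6.4, 11.4 and 13 assess risk to the participant alone. The Summary's conditional statement reaches further than the thyrotoxicosis argument behind it, and 13.1a names a second effect that this argument leaves unaddressed.

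The number of patients is small: about 1 to 4 of 224, half of them on iodide, if the assumed 0.5% to 2% is right. That assumption affects only the count; the mismatch follows from the text. The size of any fetal or infant risk cannot be judged from the protocol, and the trial's power and analysis are unaffected. This should be corrected because it concerns participant safety and costs little, but it does not threaten the trial's result.

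**What to change.** Reconcile 4.2 and 4.3 with the Summary and section 13, so that entry is limited to the population the risk assessment covers. Which route to take is a clinical decision for the sponsor:

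- **Ineligible.** State in 4.3 that pregnant and breastfeeding patients cannot enter, using the medical history that 4.3 already requires. History alone can miss an unrecognised pregnancy, so the text should say how status is established.
- **Eligible.** Say so in 4.2, add an assessment covering fetus and infant to section 13, and limit the Summary's statement about the exclusion criteria to the patients it covers.

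Under either route, section 13 should say whether the exclusions are meant to address the hypothyroidism named in 13.1a.

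The first route costs a line in an amendment and on the eligibility checklist; a few patients become ineligible and the results would not extend to them. The second costs a short added risk assessment. Neither changes the target of 224.
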